### Outcome measures

The primary outcome of interest for the clinical trial is the composite, at 3 months, of death or readmission to any Alberta acute-care hospital. Secondary outcomes of interest are the occurrence of post-discharge adverse events and adverse drug events at 1 month post discharge. Patient health status, meanwhile, will be assessed at baseline, 1 and 3 months using the Health Utilities Index
[22,23].

The elements of our composite primary outcome (i.e., death or readmission) are identified for study because these are recognized to be major events that we are ultimately trying to prevent through safer health care. The 3 month time frame is felt to be most relevant, because it is short enough to potentially relate to discharge communications, but also long enough after discharge to permit some events to accrue. The primary outcomes of interest will be assessed through existing linkages to hospitalization data from the Alberta Health Services Health Outcomes Group (for readmission to acute care hospitals), and to the Alberta Vital Statistics for post-discharge mortality. Such an approach to post-discharge outcome ascertainment avoids the shortcoming of unreliable patient self-report on readmission, and the potential challenges associated with determining vital status of patients that we are unable to reach by telephone.

The outcomes of post-discharge adverse events and adverse drug events will be determined using the method described by Forster and colleagues
[24,25]. At 1 month post discharge, a trained investigator, blinded to patient group assignments, will administer a telephone survey using a survey tool that takes approximately 15 minutes to complete to determine the post-hospital course for all consenting patients. This will allow us to determine readmission/physician visits/emergency department visits, and whether an adverse event or adverse drug event occurred. Two Royal College certified internists or College-certified family physicians, also blinded to patients’ group assignments, will independently rate the type, severity, preventability and ameliorability of all possible adverse events. Adverse events will be classified into the following types: 1. adverse drug events; 2. procedure-related injury; 3. nosocomial infection, 4. care-related fall, 5. therapeutic error, 6. diagnostic error or 7. other types. Further information on this validated multi-step method is available elsewhere
[24,25].

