### Sample size calculation and anticipated patient enrollment

As previously mentioned, a recent pilot done by the W21C team demonstrated that patients discharged from the MTU had a 23% probability of readmission to Calgary hospitals within 3 months (51 out of 219 discharged patients assessed in a pilot chart review). From this, we estimate an absolute event rate of 25% in the control group for the composite of death or readmission, and have designed our study to detect an approximately 25% relative reduction (i.e., a 6.25% absolute reduction) in the readmission rate in the intervention group. Therefore, using p_1_=0.25, and p_2_=0.1875, with alpha=0.05 and beta=0.80 in our two-tailed sample size calculation, we will require 686 patients per group. Our research plan is to enroll 700 patients per group, allowing for a safety margin for attrition. Each of the three teams usually processes an average of 2 to 4 discharges per day. As such, we anticipate that we will complete enrollment of 1400 subjects within an 18 month period and full assessment of outcomes and follow-up surveys in a 2 year period. For the secondary endpoints of post-hospital adverse events and adverse drug events, we will have adequate statistical power given that these adverse events are known to occur frequently, in approximately one quarter of patients discharged from acute-care hospitals
[1,2]. The sample size is appropriate to assess patient health status measured by HUI3 to compare two independent means for a parallel trial design, 697 patients in each group are needed to detect a clinically important difference (CID) in HUI3 overall score of 0.03 (SD=0.20).

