[28]. Furthermore, there is potential for there to be between-service differences that would affect the internal validity of the study and the comparability of the intervention and control groups. Balancing these competing concerns, and in dialogue with funding agency peer reviewers, we opted for the randomization of individual patients to intervention and control to maximize the benefits of comparability between groups.

Other challenges inherent to this study relate to acute-care physician preference and familiarity with one method for generating hospital summaries over the other, and community-care physician software incompatibilities. In a few instances, acute-care physicians may have or will develop a preference of using one system over the other. This may result in a given physician not following the patient’s assigned randomization, resulting in the exclusion of the patient and a loss of that randomization. We expect to minimize this problem by continually educating and informing the physicians of the study and the importance to adhere to the randomization assignments, as well as maintaining a strong presence throughout the MTU. More so, some community-care physicians may experience accessibility issues to the TOC summaries electronic records due to software program incompatibilities. While we foresee this as a current problem, we hope that this study will encourage the implementation of compatible programs.

This study will be one of the first to have sufficient statistical power to definitively examine the important clinical outcomes of readmission, mortality and adverse events after patients leave an acute-care facility using an electronically-based TOC communication tool. The tool that we are assessing has the potential to ameliorate a vulnerable period in health care, thus enhancing patient safety and quality of care through better communication at times of transfers of care. The tool has already been pilot tested in our jurisdiction, and through this RCT is being evaluated more broadly. This study will inform our own and other health systems globally on the potential efficacy and cost implications of such electronic communication tools. Given the widespread demand and growing investments into such electronic tools (e.g., President Obama’s $19.2 billion investment into electronic health information technology
[29]) the implications of such research are truly far reaching.

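### The 686 per group is right for the composite only; the sample-size text mislabels its power and its endpoint, and the Discussion claims power for mortality that was never calculated

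*Protocol article*

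**What the plan says.** The section on outcome measures fixes the primary endpoint: "The primary outcome of interest for the clinical trial is the composite, at 3 months, of death or readmission to any Alberta acute-care hospital".

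The sample-size section starts from pilot data in which patients "had a 23% probability of readmission to Calgary hospitals within 3 months (51 out of 219 discharged patients assessed in a pilot chart review"). On that basis, the authors write, "we estimate an absolute event rate of 25% in the control group for the composite of death or readmission". The effect to be detected is then worded as an approximate "25% relative reduction (i.e., a 6.25% absolute reduction) in the readmission rate in the intervention group". The error rates are stated as "with alpha=0.05 and beta=0.80 in our two-tailed sample size calculation". The result is 686 per group, with 700 per group to be enrolled.

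The same section argues power for adverse events and adverse drug events from their frequency, about one quarter of discharged patients, and sizes the HUI3 comparison separately. It contains nothing on mortality alone or readmission alone.

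The Data analysis section lists death or readmission as a single dichotomous outcome, and the Abstract words its power claim in the same joint way. The closing paragraph of the Discussion goes further and claims "sufficient statistical power to definitively examine the important clinical outcomes of readmission, mortality and adverse events".

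**The concern.** Three statements about the same calculation do not fit together.

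- **Power label.** Beta is the type II error rate, so a beta of 0.80 means 20% power. Either the label or the sample size must be wrong.
- **Endpoint label.** The 25% control rate is given for the composite, and 6.25 points is a quarter of that rate. Yet the sentence attaches the 6.25 points to readmission, for which the only rate in the article is the pilot's 23%.
- **Power claim.** The Discussion names readmission and mortality as outcomes the trial can examine definitively. Mortality is the rarer component, and a sample sized for a 25% event rate will not in general serve a much rarer one.

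What is at stake is interpretation. The Background criticises earlier studies for lacking power on readmission, mortality and adverse events, and the Discussion presents this trial as closing that gap. If the claim stands, a non-significant mortality difference could be read as evidence of no effect when the trial had little chance of detecting one.

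**Working it through.** **Inputs from the protocol article (sample-size section):** composite control rate p1 = 0.25; intervention rate p2 = 0.1875; two-sided alpha 0.05; 686 per group required, 700 enrolled; pilot readmission 51/219 = 23.3%, stated as 23%.

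**Assumption:** control 3-month mortality. The article gives none, so 2%, 5% and 10% are used as a range.

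**Formulas** (normal approximation, pooled variance under the null, no continuity correction), with p̄ = (p1 + p2)/2 and d = p1 − p2:

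- n per group = [1.960·√(2p̄(1−p̄)) + z_power·√(p1(1−p1) + p2(1−p2))]² / d²
- power = Φ{[d·√n − 1.960·√(2p̄(1−p̄))] / √(p1(1−p1) + p2(1−p2))}

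**Step 1. Reproduce the plan's figure.** For 0.25 against 0.1875, d = 0.0625, √(2p̄(1−p̄)) = 0.5846 and √(p1(1−p1) + p2(1−p2)) = 0.5830.

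- Power 0.80 (z = 0.842): n = 685.6, so 686. This matches.
- Power at 700 per group: 80.8%.
- Literal beta 0.80, that is power 0.20 (z = −0.842): n = 109.9, so 110.

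The 686 was therefore computed for the composite at power 0.80, and the beta label is a slip.

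**Step 2. Endpoint wording.** 25% × 0.25 = 6.25 points, the composite figure. 25% × 0.23 = 5.75 points, which would be the readmission figure from the pilot rate. The quoted 6.25 points belongs to the composite.

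**Step 3. Mortality alone, 25% relative reduction, 700 per group.**

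| Assumed control mortality | Intervention | Expected deaths per group | Power | n per group for 80% |
|---|---|---|---|---|
| 2% | 1.5% | 14 v 10.5 | 10.6% | 10,795 |
| 5% | 3.75% | 35 v 26.25 | 20.7% | 4,202 |
| 10% | 7.5% | 70 v 52.5 | 38.0% | 2,005 |

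The smallest relative reduction detectable with 80% power at 700 per group is about 81%, 56% and 41% respectively.

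**Step 4. Readmission alone, 700 per group.**

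| Reading of the target | Rates | Power | n per group for 80% |
|---|---|---|---|
| 25% relative, from 23% | 23% v 17.25% | 76.6% | 763 |
| 25% relative, from 51/219 | 23.3% v 17.5% | 77.2% | 751 |
| 6.25 points, from 23% | 23% v 16.75% | 83.5% | 639 |
| 6.25 points, from 51/219 | 23.3% v 17.0% | 83.1% | 646 |

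A 6.25-point fall from 23% is a 27% relative reduction (6.25/23), and the article says approximately 25%.

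**Step 5. Adverse events.** At the article's rate of about one quarter, with the same 25% relative reduction and full follow-up, the rates are again 25% against 18.75% and power at 700 is 80.8%.

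**The case against.** The strongest reply is that the Discussion sentence governs no analysis. The primary endpoint is the composite throughout, the Data analysis section lists no separate test of mortality, and the Abstract's power claim can be read as the composite. On that view the closing sentence is loose wording, and the other two points are slips that leave the 686 untouched. Much of this stands: the sample size is correct, and nothing in the analysis plan says that a null mortality result will be called definitive. It does not rescue the sentence itself. The sentence lists mortality as its own item, the Background uses the same list to fault earlier studies, and the economic evaluation treats lives and readmissions as separate benefits.

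A reader might also infer two stronger conclusions, which the documents do not support.

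- *That 700 per group lacks power for readmission alone.* Step 4 gives about 77% on the relative reading and about 83% on the absolute one. The first is some 3 points short of 80% and the second exceeds it.
- *That the primary test falls below 80% if the tool affects only readmission.* A figure near 74% results if readmission falls by 5.75 points and the rest of the composite is unchanged (25% to 19.25%). But the article states 6.25 points. If readmission falls by that much and nothing else changes, the composite goes from 25% to 18.75%, which is the design case. The 74% also treats the pilot's 23% as the trial's readmission rate. The pilot counted Calgary hospitals, the trial counts any Alberta acute-care hospital, and the article does not say that the step from 23% to 25% represents deaths.

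**Conclusion.** The concern holds for the mortality claim and for the two labels in the sample-size section. It does not extend to the sample size.

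- 686 per group is correct for the composite at 25% against 18.75%, two-sided alpha 0.05, power 0.80.
- The beta label is wrong as written, and the target is attached to the wrong endpoint.
- Definitive power for mortality has no calculation behind it. At the design's relative effect, power is about 11% to 38% over assumed control mortality of 2% to 10%. The exact value depends on that assumption, but it is far below 80% throughout the range.
- Readmission alone was never calculated. Its power is near 80%, so the fair criticism is that the claim is unsupported by any stated calculation, not that it is false.
- The adverse-event part of the claim has an argument in the article and is consistent with about 81% power under full follow-up.

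**What to change.** In the sample-size section, describe the target as a 6.25% absolute reduction in the composite of death or readmission, and replace the beta statement with power=0.80 (beta=0.20). In the closing paragraph of the Discussion, limit the power claim to the composite and adverse events, remove mortality from it, and make no claim of definitive power for either component alone.

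Do not add a reduced power figure for the composite: the 74% scenario depends on inputs that the article does not state.

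Neither the 686 nor the 700 per group changes, and nor does any other part of the design. The only cost is a less favourable claim in the Discussion.

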## Abbreviations

W21C: Ward of the 21^st^ Century; MTU: Medical Teaching Unit; CRU: Clinical Research Trial Unit; RCT: Randomized Controlled Trial.
